### Inclusion criteria

The inclusion criteria are as follows.
Patients undergoing continuous hemodialysis because of chronic renal failure.Patients who are expected to survive for more than 24 months after the treatment.Patients with a performance status of 0–2 [28].Patients aged 20 years and higher.Patients who provide written informed consent prior to participating in the trial.Patients with an understanding that all examinations, procedures, and treatments associated with HD will be performed per the provisions of medical care in Japan and that there is no compensation for symptoms, disease, and disorders in this trial.

Regarding inclusion criteria number 3, the scale developed by the Eastern Cooperative Oncology Group will be used to evaluate the performance status [28]. This scale is commonly used in patients with cancer; however, we used it because of the two following reasons: (1) there is no simple and useful scale to evaluate the performance status in patients with hemodialysis, and (2) it was previously used in patients with chronic dialysis [29].

### Exclusion criteria

The exclusion criteria are as follows.
Patients who already consume RJ or original bee food products.Patients who plan to consume RJ during the trial period.Patients with severe vascular diseases that need treatment.Patients allergic to RJ or original bee food products.Patients with a history of asthma or atopic dermatitis.Pregnant or lactating patients.Patients who are judged as unsuitable for inclusion in the trial by the principal investigator or co-investigators.

### Primary endpoint

The primary endpoint is the change in FMD before treatment and 24 months after treatment initiation.

### Secondary and other endpoints

The secondary and other endpoints are as follows.
FMD at 0, 3, 6, 9, 12, 15, 18, and 21 months after treatment initiation.Aortic calcification index (ACI) at 0, 12, and 24 months after treatment initiation.ESC count in the blood at 0, 3, 6, 9, 12, 15, 18, 21, and 24 months after treatment initiation.Serum levels of vascular endothelial growth factor (VEGF), MCSF, 8-hydroxydeoxyguanosine (OHdG), and malondialdehyde (MDA) at 0, 3, 6, 9, 12, 15, 18, 21, and 24 months after treatment initiation.Incidence of cardiovascular diseases, cerebrovascular diseases, and stenosis of blood access during the 24 months.Adverse events of oral intake of RJ.

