**Methods:**

This will be a multicenter, prospective, double-blind, randomized controlled trial. We will enroll 270 participants at Nagasaki Jin Hospital, Shinzato Clinic Urakami, and Maeda Clinic, Japan. The participants will be randomized into RJ and placebo groups. The trial will be conducted according to the principles of the Declaration of Helsinki, and all participants will be required to provide written informed consent. The RJ group will be treated with 3600 mg/day of RJ for 24 months, and the placebo group will be treated with starch for 24 months. The primary endpoint will be the change in flow-mediated dilation (FMD), a parameter of endothelium function, from the time before treatment initiation to 24 months after treatment initiation. The secondary and other endpoints will be changes in FMD; ESC count; serum levels of vascular endothelial cell growth factor, macrophage colony-stimulating factor, 8-hydroxydeoxyguanosine, and malondialdehyde; the incidence of cardiovascular diseases, cerebrovascular diseases, and stenosis of blood access; and safety.

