### Randomization

Randomization will be performed by an independent employee of Nagasaki University Hospital using the envelope method, and medical investigators at each institute will be responsible for allocating patients. In short, eligible patients will be randomly assigned in a 1:1 ratio using a computerized random number generator, and the allocation information will be placed in sealed envelopes. Each patient will be assigned a unique number to protect their personal information. The randomized list will be managed by only an independent data manager and will be concealed from all investigators and patients. All information regarding patient selection will remain confidential and unknown to all investigators, including outcome assessors and statisticians, until the completion of the trial. Emergent unblinding will not be possible in this trial.

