### Cardiovascular diseases, cerebrovascular diseases, and stenosis of blood access

Regarding cardiovascular diseases, new onset of ischemic heart disease and arrhythmia requiring medical treatment will be recorded. With regard to arrhythmia, frequent arterial or ventricular premature beats, supraventricular or ventricular tachycardia, and atrial fibrillation will be evaluated. In addition, the frequencies of hypertension, hypotension, and new-onset arrhythmia will be recorded. Hypertension and hypotension are defined as systemic blood pressures > 160 mmHg and < 80 mmHg, respectively. Cerebrovascular diseases include cerebral hemorrhage, cerebral infarction, and subarachnoid bleeding. Stenosis of blood access is defined as new-onset stenosis requiring balloon dilation and/or surgery.

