### Safety management

If serious adverse events (SAEs) that are speculated to be associated with oral RJ intake, RJ administration will be discontinued. In case of the existence of a causal relation between SAEs and RJ, this study will be terminated. Judgments about RJ-related SAEs will be made by medical investigators at each institute and will be reported to the ethics committee within 24 h and to the coordinate centers within 3–5 days (3 working days). If mild adverse events occur, RJ administration will be discontinued until recovery. In this study, changes in drug dose will not be permitted. On the other hand, RJ administration and all examinations will be terminated in case of participant withdrawal. In addition, the principal investigator (YM) must decide to terminate the trial even if one investigator suggests early termination because of SAEs.

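### The safety endpoint is worded as events of royal jelly intake, which does not fit the placebo arm and is narrower than the abstract's plain safety endpoint; it should be all adverse events, compared by randomised arm

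*Protocol article*

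**What the plan says.** The Protocol article describes safety in several places, and not in the same terms.

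- **Abstract, Methods.** The endpoints end with "the incidence of cardiovascular diseases, cerebrovascular diseases, and stenosis of blood access; and safety". Safety carries no causal restriction here.
- **Secondary and other endpoints.** The corresponding item is "Adverse events of oral intake of RJ". The same list separately includes "Incidence of cardiovascular diseases, cerebrovascular diseases, and stenosis of blood access during the 24 months", with no attribution condition.
- **Cardiovascular diseases, cerebrovascular diseases, and stenosis of blood access.** Besides defining those events, this section says that "the frequencies of hypertension, hypotension, and new-onset arrhythmia will be recorded", again without attribution.
- **Safety management.** "Judgments about RJ-related SAEs will be made by medical investigators at each institute". The surrounding text concerns discontinuation, reporting and termination. The rule for milder events has no relatedness condition: "If mild adverse events occur, RJ administration will be discontinued until recovery".
- **Randomization.** Allocation is to stay "unknown to all investigators, including outcome assessors and statisticians, until the completion of the trial", and "Emergent unblinding will not be possible in this trial".
- **Statistical analyses.** Other variables and data are to be analysed in the same way as flow-mediated dilation, that is, between groups at fixed months. Adverse events are not named.

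**The concern.** An endpoint limited to events of RJ intake has two weaknesses in a placebo-controlled trial. First, it has no proper meaning for patients on starch: the endpoint is either empty in that arm by definition or becomes a count of events that somebody thought looked product-related. Second, that opinion has to be formed without knowing the allocation, in hemodialysis patients followed for 24 months, for whom the underlying illness often offers another explanation.

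Randomisation makes the opinion unnecessary. With concurrent placebo patients, an excess of events on RJ shows in the arm totals whether or not anyone recognised the cause. The events at stake are those outside the vascular, access, blood-pressure and rhythm categories, for example gastrointestinal symptoms, infection or allergic reactions. The protocol itself treats allergy as relevant, since it excludes patients with bee-product allergy, asthma or atopic dermatitis. If only attributed events were reported, a statement that RJ was safe would rest on unverifiable judgements and not on the randomised comparison.

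**Working it through.** The article states no adverse event rate, no safety sample size and no safety power, so there is no safety figure to reproduce. The main check is textual.

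**1. Scope in the two endpoint statements.** The abstract says safety; the endpoint list says events of RJ intake. The second is narrower on its face. Nothing states which governs.

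**2. Applicability to both arms.** Study design gives the placebo group starch for 24 months. Taken literally, the listed endpoint cannot occur in that group.

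**3. Who could attribute.** The only causality process described is that of the site investigators, for SAEs. Under Randomization they are blinded until completion. For non-serious events no attribution process is described.

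**4. What is already counted whatever the cause.** Ischemic heart disease, arrhythmia, cerebrovascular disease, access stenosis, hypertension and hypotension. For these no attribution is needed.

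**5. What remains.** For all other adverse events, and for SAEs overall, no comparison by arm irrespective of cause is named.

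**6. Is an all-cause comparison feasible?** Inputs: n = 135 per arm (Sample size) and two-sided alpha 0.05 (the article gives 0.05 without sidedness; two-sided is assumed). The placebo event rates p0 are assumptions, shown over a range; p1 is the RJ rate.

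Power = Φ[(|p1 − p0| − 1.96·s0)/s1], where s0 = √(2·p̄(1 − p̄)/n), p̄ = (p0 + p1)/2, and s1 = √((p0(1 − p0) + p1(1 − p1))/n).

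For example, with p0 = 0.30 and p1 = 0.466: p̄ = 0.383, s0 = 0.0592, s1 = 0.0583, and (0.166 − 1.96 × 0.0592)/0.0583 = 0.86, which gives power of 0.80.

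| Assumed placebo rate | Smallest RJ rate detectable at 80% power | Excess (points) |
|---|---|---|
| 5% | 15.3% | 10.3 |
| 10% | 22.6% | 12.6 |
| 20% | 35.2% | 15.2 |
| 30% | 46.6% | 16.6 |
| 50% | 66.8% | 16.8 |
| 70% | 84.3% | 14.3 |

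With a 20% loss (135 × 0.8 = 108 per arm) the detectable excess is 11.9 to 18.7 points over the same placebo rates.

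**7. Does attribution always hide harm?** Assume true all-cause rates of 30% against 44%, so 14 points are caused by RJ; all-cause power is 67%. Let a share s of RJ-caused events be recognised and a share f of background events be wrongly attributed. The attributed rates are then 0.30f on placebo and 0.30f + 0.14s on RJ.

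- s = 0.3, f = 0.2: 6.0% against 10.2%, power 24%.
- s = 0.8, f = 0.05: 1.5% against 12.7%, power 95%.

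Attribution can therefore lower or raise the chance of detecting harm, depending on accuracy that the trial cannot check.

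**The case against.** The strongest reply is that the listed wording is loose and does not restrict anything. It does not use related, attributed or judged, and could mean adverse events while taking study product. The article elsewhere uses RJ administration for study product in both arms (Safety management, Statistical analyses), and the abstract's plain safety supports the broader reading. A condensed article may also leave adverse event collection and tabulation to the full protocol, which is not shown. All of this is fair, and it limits the weight of the point. It does not remove it: the endpoint as worded is a statement and not an omission, and a plain reading of it is the narrow one.

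A reader might infer more than the documents support:

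- *That the site judgements under Safety management define the endpoint.* They are described for SAEs only, for stopping and reporting; nothing says that they select events for the endpoint.
- *That events judged unrelated go unrecorded.* No section says so, and the rule for mild events has no relatedness condition.
- *That the trial makes no comparison irrespective of cause.* Several major clinical outcomes, including hypotension, are counted without attribution, and other data are to be analysed between groups.
- *That assessors are told beforehand that RJ is safe.* The remark on its safety belongs to the sample size justification and does not instruct assessors.

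**Conclusion.** The point holds as a wording defect with a practical consequence. The endpoint list ties safety to RJ intake, the abstract does not, and the literal version neither fits the placebo arm nor avoids dependence on blinded attribution. Apart from the events already counted whatever their cause, no all-cause comparison by arm is named.

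The weight is minor to moderate. There is no numerical error, and no bias of known size or direction can be claimed: step 7 shows that attribution could help or hurt. The case for the change is that a randomised comparison of all events needs no unverifiable judgement. It would be informative for excesses of roughly 10 to 17 points at full enrolment, under the assumed placebo rates and a two-sided 5% level; smaller excesses would probably be missed. If the full protocol already defines safety as all adverse events in both arms, only the article's wording needs correcting.

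**What to change.** Reword the item under Secondary and other endpoints so that the safety endpoint is all adverse events and all serious adverse events in both arms, from first intake of study product to 24 months, whatever the judged cause, tabulated and compared by randomised arm. Show the investigators' blinded causality judgement as a supportive display only. Use the same definition in the abstract.

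The cost is a change of wording and somewhat more event entry at the sites. No extra visits are needed, since Follow-up says that patients attend 3–4 times per week for dialysis.

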### Follow-up

The patients will visit the hospital 3–4 times per week for maintenance HD. The frequency of HD in a week will be determined by medical judgment based on laboratory data, clinical practice, and patient wishes. Similarly, decisions about the contents of HD will be made according to each institution’s policy independent of this trial. There are no relevant concomitant care and interventions that are permitted or prohibited during the trial.

### Sample size

Unfortunately, there are no reports on changes in FMD due to oral intake of RJ in HD patients. In addition, temporal changes in FMD during HD sessions are unclear. There is general agreement that RJ is a safe food, and our study design poses an extremely low risk to patients as the only other invasive intervention will be the collection of a blood sample (20 ml) every 3 months. Considering these aspects, the proposed sample size was calculated according to the expected agreement rates (60%) of patients, which is the object of this trial. Finally, 135 patients will be enrolled in each of the two groups. For recruitment, the posters that showed purpose, method, risk, and cost are displayed. All authors will obtain written informed consent from potential trial participants or authorized surrogates after oral explanation and providing the explanatory documents. The consent form is original, and it has been approved by our IRB.

We also calculated the proposed sample size according to a previous paper on FMD in HD patients and a meta-analysis of changes in FMD associated with the oral intake of another supplement (magnesium) [30, 31]. In short, 112 patients will be enrolled in each group (a total of 224 patients) with an alpha error rate of 0.05 and a power of 0.8. This is because incomplete data may be available for some patients (approximately 20% of the patients), and patient dropouts may occur before the completion of the trial. Finally, we plan to enroll 135 patients in each group. Regarding such processes, we have had repeated discussions with several biostatisticians. In addition, our decision on sample size was reviewed twice by IRB members, including other biostatisticians. Finally, this policy was approved by IRB because of limited information about the influence of RJ on FMD and the high safety of RJ.

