### Statistical analyses

The results of all examinations will be expressed as mean ± SD. To clarify the primary endpoint, the changes in the rates of FMD after treatment for 24 months (FMD for 24 months/baseline) will be compared between the RJ and placebo groups using the Student’s *t* test. Non-adherence and missing data will not be used in this analysis. A similar analysis will be performed to compare the changes in FMD at 6, 12, and 18 months between the two groups. For this analysis, missing data will be used according to the period of RJ administration. Other variables and data will be analyzed similarly at 6, 12, 18, and 24 months. There is no plan for any additional analyses. Permitted investigators (KO, YM, TM, KM) will have access to these interim results.

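### If 112 per group is the evaluable number, enrolling 135 leaves 108 after the stated 20% loss (power about 78.5%, not 80%), and the text does not say which losses the 20% covers

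*Protocol article*

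**What the plan says.** The Sample size section of the protocol article gives two bases for the trial's size.

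- The first is consent: "the proposed sample size was calculated according to the expected agreement rates (60%) of patients". This leads to 135 per group.
- The second is a power calculation that draws on published FMD data: "112 patients will be enrolled in each group (a total of 224 patients", "with an alpha error rate of 0.05 and a power of 0.8". The next sentence gives as a reason that "incomplete data may be available for some patients (approximately 20% of the patients), and patient dropouts may occur before the completion of the trial". The conclusion is: "Finally, we plan to enroll 135 patients in each group".

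The assumed difference in FMD, its standard deviation and the sidedness of the test are not given; only the sources are cited.

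The Statistical analyses section compares the groups on the primary endpoint with Student's t test and adds: "Non-adherence and missing data will not be used in this analysis".

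**The concern.** Two different numbers per group are both described as the number to be enrolled, and only one of them is tied to a power. If 112 is the number needed in the analysis, 135 should be large enough to leave 112 after the expected loss, and it is not.

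The loss allowance is also undefined. The 20% is attached to incomplete data. Dropouts are mentioned beside it without a rate, and non-adherence is not mentioned in the Sample size section at all, although the primary analysis excludes it.

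What is at stake is whether the 80% can be read as a property of the trial as it will be analysed.

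**Working it through.** **Inputs**

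- From the Sample size section: 112 per group, alpha 0.05, power 0.8, loss of about 20%, enrolment of 135 per group.
- From the Randomization section: 1:1 allocation.
- From the Statistical analyses section: a two-sample t test, with non-adherent patients and missing data excluded.
- Assumed here: a two-sided test, because the article does not state sidedness.

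**Step 1. From 112 to 135**

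- To keep n after a loss fraction L, enrol n/(1 − L): 112/(1 − 0.20) = 140 per group. This does not give 135.
- Multiplying instead: 112 × 1.20 = 134.4, which rounds up to 135. The stated figure is consistent with this step, but the article does not describe it.

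**Step 2. What 135 leaves**

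- 135 × (1 − 0.20) = 108 per group, which is 112 − 108 = 4 short (4/112 = 3.6%).
- The largest total loss that still leaves 112 is 1 − 112/135 = 17.0%.

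**Step 3. Power at 108**

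- The standardised difference has to be back-calculated. With 112 per group, two-sided 0.05 and 80% power, the noncentral t distribution gives d = 0.376. The normal approximation gives √(2/112) × (1.960 + 0.842) = 0.374.
- At 108 per group, power is 78.5% by the t calculation and 78.6% by the normal approximation.
- If the test were one-sided at 0.05, with d again back-calculated from 112, power at 108 would be 78.7%. The sidedness assumption hardly matters.

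**Step 4. Losses beyond 20%**

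- The article gives no rate for non-adherence and no separate rate for dropout.
- As an illustration only, a further 5 percentage points would leave 135 × 0.75 = 101.25, about 101 per group, with power of about 76%.

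**Step 5. The other reading of 112**

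- If 112 is an enrolled number that already contains the 20%, the evaluable requirement is 112 × 0.8 = 89.6, about 90 per group.
- The 108 left from 135 would then exceed the requirement, with power of about 87%. Going on to 135 for the same reason would apply the allowance twice.

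**The case against.** The strongest defence is the order of the sentences. The one that gives the 20% follows directly on 112 and is worded as the reason for it. Read literally, 112 already includes the loss, about 90 are needed, and 108 evaluable patients give about 87% power, so there is no shortfall. This reading cannot be excluded. It fits less well, because it leaves the further step to 135 without a reason, and the text would still need correcting.

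A second defence is size. The 20% is approximate, 135 holds 112 at 17.0% loss, and the deficit is 4 patients and about 1.5 power points. This stands: the inflation step alone does not make the trial materially underpowered.

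A third is that 135 is first attributed to the agreement rate, with the power calculation presented as an additional one. So a reader who infers that 135 was certainly produced by multiplying 112 by 1.2 goes further than the text. The match is exact after rounding up, but the step is not stated. The agreement rate, for its part, says nothing about power and cannot support the 80%.

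A reader might also infer that power will fall far below 80% once non-adherent patients are removed. The documents do not support any such figure. They give no non-adherence rate, and the 20% may partly or wholly include dropouts and non-adherent patients. Only the direction is certain: any exclusion beyond 20% lowers power further.

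**Conclusion.** The point holds as a small inconsistency in stated figures together with an undefined loss allowance. On the more natural reading, where 112 is evaluable, the plan's own 20% loss leaves 108 per group and power of about 78.5%, and the stated 80% needs total loss of 17.0% or less. This rests on a two-sided t test and on a standardised difference of 0.376 back-calculated from 112. The 112 itself cannot be checked, because the difference and SD behind it are not printed.

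On the alternative reading the power is adequate, but the section counts the loss twice. Either way, the section does not establish what power the analysed sample has. How much the non-adherence exclusions would cost cannot be determined from the article.

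**What to change.** Rewrite the Sample size paragraph without adding patients:

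1. Label 112 per group as the evaluable number for 80% power and 135 as the number randomised.
2. State that 20% total loss leaves 108 evaluable per group, with power of about 78.5% for the difference that 112 was designed to detect.
3. If 112 already includes the 20%, give the evaluable number instead (about 90) and remove the second inflation.
4. Say that the loss allowance has to cover missing data, dropout and the non-adherence exclusions of the primary analysis together.
5. Present the 60% agreement rate as evidence of feasible recruitment only, not as a basis for power.

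The cost is one rewritten paragraph and, on the more natural reading, a power figure about 1.5 points lower.
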